## Abstract

**Objectives:**

To evaluate the effectiveness of an innovative supervised exercise programme to mitigate the loss of lean body mass, functional capacity and quality of life in people with head and neck cancer, as well as to identify the optimal moment to apply it, before or after radiotherapy treatment, compared with the prescription of a physical activity plan carried out autonomously.

**Methods:**

Patients with squamous cell carcinoma of the head and neck (*n* = 144), treated with radiotherapy, will be randomly assigned to one of 3 comparison groups: pre-radiotherapy supervised exercise, post-radiotherapy supervised exercise and autonomous exercise, stratifying by human papillomavirus infection and previous surgery.

The exercise programme will be carried out in 36 sessions over 12 weeks, combining moderate and high intensity strength and aerobic exercises. The main outcome variable is the change in lean body mass at 6 months measured by bioimpedance, while secondary variables are functional capacity, symptoms, quality of life and adverse effects. Longitudinal generalised mixed models will be used for the analyses of the repeated measurements at 3, 6, and 12 months after baseline.

**Conclusions:**

The pilot study supports the feasibility and safety of the project. However, as the programme progressed, attendance at the sessions decreased. Strategies will be necessary for increasing attendance, as well as involving the patient in their recovery and other incentives. Follow-up after treatment to assess acute/late toxicity will enable us to know the response to both the exercise programme and its adherence.

**Trial registration:**

NCT04658706 Date and version identifier: March 1, 2023. Version 1.1

## Introduction

Head and neck cancer (HNC) was the seventh most frequently diagnosed cancer worldwide in 2020 [1]. The main risk factors that cause this type of cancer to develop are smoking, alcoholism, diet, sedentary lifestyle, obesity and human papillomavirus (HPV) infection, among others [2]. This unhealthy background added to both the disease and its treatments effects tremendously reduce cardiorespiratory capacity, lean body mass (through accelerated processes of cachexia and sarcopenia) bone mass, and provoke psychosocial distress, depression, pain, fatigue, and impaired cognitive function [3].

Between 30 and 50% of HNC patients have malnutrition and it has been estimated that they may experience 5–10% weight loss during radiotherapy treatment [4, 5]. Weight loss of more than 5% has been associated with a decrease in overall and specific survival for head and neck cancer. In addition, it is estimated that more than 70% of weight loss can be attributed to loss of lean body mass, which leads to a decrease in strength, functional capacity and quality of life [6]. Because of that lean body mass is considered an appropriate and feasible end point in clinical trials of HNC. Additionally, sarcopenia before and after treatment is an independent factor of poor prognosis associated with decreased survival in patients undergoing radiotherapy with curative intent [7]. Moreover, sarcopenia has recently been associated with increased acute toxicity (grade ≥ 3 dysphagia) [8] and decreased progression-free survival [9]. For this reason, it is deemed appropriate to perform body composition measurements as part of the diagnosis and evaluation of interventions for HNC [10–12].

Nutritional approach is a fundamental part of support for these patients. Nutritional interventions through oral supplements and dietary advice have shown short-term benefit in patients with HNC [13]. Patients with head and neck tumours represent a group with a high prevalence of malnutrition and with very specific side effects compared to other types of tumours, which can cause loss of lean body mass [8]. Most studies have explored the impact of either nutritional supplements or physical exercise (PE) separately. Therefore, it seems necessary to explore the benefit of nutritional intervention and PE jointly in these patients and their impact on lean body mass. Up to now, randomised studies that have assessed the impact of a PE programme in these patients are scarce [14–17], and have limitations in their applicability since they have not included a control arm or the PE has not been supervised [14, 15], nor performed using a progressive overload programme to optimise lean body mass gain [16]. The most recent Head and Neck Cancer Survivorship Consensus guidelines establish that further research is needed on the implementation of physical activity promotion in routine clinical care and the optimal timing, intensity and duration of exercise intervention in relation to oncological treatment, as well as research on the links between exercise and HNC recurrence or survival [18].

In this context, this study aims to evaluate the effectiveness of an innovative supervised PE programme to mitigate the loss of lean body mass, improve functional capacity and quality of life, which are dramatically reduced in people diagnosed with head and neck cancer; to compare it with the prescription of PE carried out independently; and to identify the optimal moment to apply this programme: before (prehabilitation) or after radiotherapy treatment.

## Methods/design

### Trial design

The SEHNeCa project is a multicentre, randomised, controlled clinical trial with three arms. Patients are recruited by the radiation oncologist at the patient’s first visit to the radiation oncology department, where they are asked to participate in the programme. Four assessments are made of all the participants, regardless of the group they belong to, at 0, 3, 6 and 12 months.

The baseline assessment will be performed during the same week as recruitment. After randomisation, the pre-radiotherapy group will start the supervised PE programme (at least 7–10 days before starting radiotherapy). The control and post-radiotherapy groups will initially receive physical activity guidelines that they can perform independently. The post-radiotherapy group will start supervised training 4–6 weeks after finishing radiotherapy and the control group will not have supervised training.

All the patients will receive follow-up by the endocrinology service (before radiotherapy, during radiotherapy, at the end of radiotherapy and one month, 3 months, 6 months and 12 months after the end of radiotherapy) in which they will receive screening and assessment of nutritional status as well as individualised nutritional intervention following international guidelines [19], which may include nutritional advice, oral nutritional supplementation, and/or insertion of a feeding tube as required by each patient (Table 1) (Fig. 1).

**Table 1 Tab1:** SEHNeCa Programme timeline

Follow up	D0	W1	W2		W3		W4		M2		M3		M4	M5	M6	M7	M12	M18
**Diagnosis and recruitment**	**X**																	
**Nutritional evaluation**		**X**									**X**				**X**		**X**	**X**
**Radiation oncology evaluation**	**X**										**X**		**X**		**X**		**X**	**X**
**Radiotherapy**					X													
**Measurements**		**X**											**X**			**X**	**X**	
**Supervised Exercise Intervention**			**PRE-RADIOTHERAPY GROUP**															
													**POST-RADIOTHERAPY GROUP**					
**Autonomous Exercise Intervention**			**Control Group and Post-radiotherapy Group**										**Pre-radiotherapy Group and Control Group**					

*D* Day, *W* Week, *M* Month

**Fig. 1 Fig1:**
[figure not shown]
Flow diagram. *PVS* Prescribe Vida Saludable

To achieve both these objectives, the radiotherapy-oncology and endocrinology departments of Basurto University Hospital, Cruces University Hospital and Galdakao Hospital have collaborated.

### Participants

*Inclusion and exclusion criteria* (Table 2).

**Table 2 Tab2:** Inclusion/Exclusion criteria

Inclusion criteria	Exclusion criteria
Diagnosis of carcinoma of the larynx (except T1-T2 N0 of the glottis), pharynx, oral cavity, salivary gland, paranasal sinuses, or cervical metastasis of unknown origin in stages I-II-III-IVa-IVb	Decompensated heart disease, uncontrolled hypertension (SBP > 200 or DAT > 110), heart failure (NYHA > I), or constrictive pericarditis
Radiotherapy (with or without concomitant chemotherapy) preceded or not by surgical treatment and performed with radical intent	**Medical contraindication against exercise** (such as bone fractures, tendon ruptures, spondylolisthesis > 25% with neurological compromise, rhabdomyolysis, herniated disc in the spine with neurological symptoms, cardiovascular comorbidities such as unstable angina, current myocarditis or thrombophlebitis); Neutropenia (< 500 mm3), severe anaemia (Hb < 8.0 g/dl), platelet count < 50.000 microL
> 18 years	Radiotherapy with palliative intent
BMI > 18.5	Pregnancy
ECOG 0–1 or Karnofsky Index ≥ 80%	**Regular physical activity** (150 min/week of moderate activity or 75 min/week of vigorous activity, including two or more weekly strength training sessions), as measured by the PVS questionnaire
Signed consent form	Carcinoma of the glottis (T1-T2, N0)

*T*_*(1–2)*_ Tumour (TNM classification), *N*_*(0)*_ Node (TNM classification), *SBP* systolic blood pressure, *DAT *Diastolic blood pressure, *NYHA* New York Heart Association, *Hb* Haemoglobin, *BMI* Body Mass Index, *ECOG* Eastern Cooperative Oncology Group, *PVS* Prescribe Healthy Life

### Randomisation

Randomisation is carried out on a central basis through the coordinating committee. This will be made up of the organization responsible for the study’s management and the researchers. The committee will be blind to the assignment of patients in the comparison groups and will convene in the Primary Health Research Unit of Bizkaia.

The 120 patients included in the study will be randomly assigned and consequently registered and attached to one of the three study groups in a 1:1:1 ratio, through randomisation by random blocks of 3 or 6 patients. Patients are stratified according to HPV status and previous surgery yes/no.

### Evaluation

Evaluation of the SEHNeCa exercise programme involves measuring the safety, adherence, and effectiveness of the programme. These analyses incorporate elements of the reach, effectiveness, adoption, implementation, and maintenance (RE-AIM) framework [20].

### Safety

The incidence and severity of any adverse events (e.g. falls or muscle strains) that occur during the health-centre based sessions will be monitored and reported by the supervising exercise physiologist/nurse using programme-specific documentation.

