### Adherence

Attendance at health-centre based exercise sessions and the reason for any missed sessions will be tracked throughout the programme. Further, completion of assessments at pre-programme and post-programme time points as well as follow-up questionnaires will be reported on.

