### Autonomous exercise intervention

Every patient in the control group will receive the corresponding standard treatment (i.e. radiotherapy), determined by the regular oncological consensus committee. In addition, they will receive a prescription concerning healthy lifestyles and a personalised exercise plan, together with an evaluation and individualised nutritional intervention by a physician at the Endocrinology and Nutrition department in Cruces, Basurto or Galdakao Hospitals, in the same way as for intervention groups. They will also be evaluated in the radiation oncology department with the routine follow-up (end of radiotherapy, one, three, six and twelve months after radiotherapy) to assess outcomes and toxicity due to oncological treatment according to Radiation Therapy Oncology Group and Common Terminology Criteria for Adverse Events (vs 5.0) toxicity criteria.

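### Exercise-related adverse events and exercise adherence are captured only in supervised sessions, so neither can be compared with the autonomous arm

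*Protocol article*

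**What the plan says.** Two short sections of the protocol article set the capture rules. Under Safety, the rule is that "adverse events (e.g. falls or muscle strains) that occur during the health-centre based sessions will be monitored and reported by the supervising exercise physiologist/nurse". Under Adherence, "Attendance at health-centre based exercise sessions and the reason for any missed sessions will be tracked throughout the programme"; the only other item there is whether assessments and follow-up questionnaires were completed.

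The Trial design section says that "the control group will not have supervised training". Controls are nevertheless meant to exercise: under Autonomous exercise intervention, "they will receive a prescription concerning healthy lifestyles and a personalised exercise plan". The supervised arms also have autonomous periods. For the start of the trial, Trial design says: "The control and post-radiotherapy groups will initially receive physical activity guidelines that they can perform independently". Table 1 later places the pre-radiotherapy arm on autonomous exercise, together with controls.

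The Abstract (Methods) lists harm among the trial's outcomes: "secondary variables are functional capacity, symptoms, quality of life and adverse effects". It does not say whether the last item means exercise events, treatment toxicity or both.

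**The concern.** The trial sets supervised exercise against exercise prescribed for patients to do alone. Two natural questions are whether supervision changes the risk of exercise injury and how much exercise each arm did. The stated rules can answer neither for the autonomous arm, because they record only what happens in a setting that controls never enter. Injuries at home, or that appear after a session, are missed in every arm.

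Two things are at stake. First, if session events were set beside the control arm's count, supervision would look more harmful simply because it is watched, and harm from unsupervised exercise would go unseen. Second, without a record of autonomous activity, the trial could not describe what the comparator arm did. That would help to explain a lean-mass result in either direction, especially as the Discussion reports falling attendance in the pilot.

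**Working it through.** The plan gives no figure for this point, so there is none to reproduce. The check is of coverage, followed by one illustration.

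**1. Coverage by arm and phase** (Trial design, Table 1, Safety, Adherence, Autonomous exercise intervention)

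| Arm and phase | Exercise | Exercise events recorded | Exercise recorded |
|---|---|---|---|
| Pre-radiotherapy, 12-week programme | supervised | in sessions only | attendance |
| Pre-radiotherapy, later | autonomous | none | none |
| Post-radiotherapy, initial | autonomous | none | none |
| Post-radiotherapy, 12-week programme | supervised | in sessions only | attendance |
| Control, throughout | autonomous | none | none |

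**2. Recorded time at risk**

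The Abstract (Methods) states: "The exercise programme will be carried out in 36 sessions over 12 weeks", that is 36 / 12 = 3 sessions a week. The section on the supervised intervention gives two weekly sessions of 1 to 1.25 h and a third of 30 to 45 min.

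- Lower end: 2 × 1 + 0.5 = 2.5 h a week; × 12 = 30 h.
- Upper end: 2 × 1.25 + 0.75 = 3.25 h a week; × 12 = 39 h.
- Control: 0 sessions, 0 h.

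A fully attending supervised patient thus has 30-39 h of recorded time within 12 months of follow-up. For controls, the expected recorded count is (true rate) × 0 h = 0 at any true rate.

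**3. Other data that might fill the gap**

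- Radiation oncology follow-up of controls uses RTOG and CTCAE version 5.0 criteria, but its stated purpose is toxicity from the oncological treatment. Falls and strains from exercise are not mentioned.
- The listed questionnaires (SF-36, QLQ-C30, H&N-35, SPADI) cover quality of life, symptoms and shoulder pain and disability. None is described as recording injuries or exercise done.
- The PVS questionnaire measures physical activity, but its only stated use is the exclusion criterion in Table 2.

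**4. Illustration: what a naive comparison would show**

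Assumptions, none taken from the documents except the 48 per arm: the same true proportion p of patients with an exercise event in both arms; all events in the supervised arm fall in sessions (an upper bound); no drop-out; control count fixed at 0; two-sided Fisher test at 0.05.

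The smallest supervised count significant against 0 of 48 is 6. For 6 against 0, the p-value is 2 × (48·47·46·45·44·43)/(96·95·94·93·92·91) = 0.026. For 5 against 0 it is 2 × (48·47·46·45·44)/(96·95·94·93·92) = 0.056. The chance of a spurious excess is therefore P(X ≥ 6) with X ~ Binomial(48, p).

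| p | Expected supervised count, 48p | Control | Chance of a spurious p < 0.05 |
|---|---|---|---|
| 5% | 2.4 | 0 | 3% |
| 10% | 4.8 | 0 | 35% |
| 20% | 9.6 | 0 | 94% |

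The plan states no such test. The table shows only why session counts must not be set against the control arm's zero.

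**The case against.** The strongest reply is that the Safety and Adherence sections describe delivery of the programme. The Evaluation section introduces both as evaluation of the exercise programme within the RE-AIM framework, and no passage states a between-arm test of session events. The secondary outcome in the Abstract may well mean treatment toxicity, which is assessed in controls. The document is also a journal article: the fuller protocol and operational manuals may contain more, and the flow diagram, whose legend expands PVS, could not be seen.

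Much of this stands. No planned analysis is shown to be biased, and the secondary outcome cannot be said to contradict the Safety section. What does not stand is the appeal to condensation as regards exercise events. The article does not merely omit how they are recorded; it states a rule that confines recording to health-centre sessions. For autonomous activity the position is softer: the article names session attendance and describes no other exercise measure during follow-up.

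A reader might infer more: that safety as a whole, or supervised against autonomous exercise as such, cannot be compared. The documents do not support that. Lean body mass, function and quality of life are assessed in all participants at 0, 3, 6 and 12 months, and groups are compared by intention to treat, which needs no exposure data. The objective's comparator is the prescription of an autonomous plan, so a null result would still answer the stated question; exposure data would help to explain it.

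**Conclusion.** The point holds for two measures only. Under the stated rules, exercise-related adverse events and exercise adherence are captured for about 30-39 hours per fully attending supervised patient and for 0 hours per control, and the autonomous phases of both supervised arms are uncovered. A fair comparison of exercise-related harm and a description of the exercise done in the comparator arm are lost. The randomised comparison of lean body mass, function and quality of life and the assessment of oncological treatment toxicity are unaffected.

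The hours rest on the stated session lengths and full attendance; the 3%, 35% and 94% rest on assumed rates and an unplanned test, and are illustrative only. The conclusion also assumes that no fuller document adds all-arm capture. This is an inexpensive improvement worth making, and does not threaten the primary result. Timing matters: the article reports 71 of 144 patients already included (71/144 = 49%), and data for visits already past cannot be collected as they fell due.

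**What to change.** At the existing 3, 6 and 12 month assessments, in all three arms:

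- Use one identical short form for falls, musculoskeletal injuries and other exercise-related events since the last visit, whether in or out of sessions.
- Repeat the PVS physical-activity questionnaire already used at eligibility.

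In the Safety section, state that any between-arm comparison of exercise events rests on that form only, and that session-recorded events are reported separately as a description of the supervised programme. In the Abstract and the outcome sections, say whether the secondary outcome of adverse effects means exercise events, treatment toxicity or both.

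The cost is one new form, one questionnaire already in use and a few minutes at visits already planned. No treatment, visit or primary analysis changes. The downsides are that the answers depend on recall, and that data will be missing for assessments already past.

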### Adherence

Attendance at health-centre based exercise sessions and the reason for any missed sessions will be tracked throughout the programme. Further, completion of assessments at pre-programme and post-programme time points as well as follow-up questionnaires will be reported on.

### Effectiveness: primary study outcomes

Change in Lean Body Mass (kg), measured by using an Inbody 770 bioimpedance analyser (In-body, Seoul, Korea).

### Effectiveness: secondary study outcomes

#### Anthropometry and body composition

Height will be measured using a wall stadiometer, and body composition with a bioimpedance analyser. BMI (body mass index) (kg/m2), skeletal muscle mass (kg), fat free mass (kg); bone mineral content (kg), body fat mass (kg), body fat percentage (%), intra and extracellular water (l); extracellular water/total body water, visceral fat (cm2), basal metabolic rate (kcal) and phase angle (º) will be registered. Abdominal and waist circumference will be taken [21].

#### Physical function

Physical function is assessed by 400-m walk tests in a 20-m corridor in a controlled environment (temperature, 20-21º C; relative humidity, 50–55%; barometric pressure, 755–765 mmHg). The participants will be seated for measuring heart rate and blood pressure before and after the test. The repeat chair stand test (5 times sit to stand test), the handgrip dynamometry test and the Timed Up and Go (TUG) test will be carried out.

Maximal strength in the upper and lower body will be measured in terms of the 5-repetition maximum (5RM) test (the maximum load that can be lifted five times) in chest press, seated rowing and leg extension, respectively. These assessments are to be conducted by an independent exercise physiologist not involved with administering the exercise intervention.

#### Patient-reported outcomes

A series of questionnaires with sound psychometric properties are to be used to assess general health and cancer-specific quality of life at baseline and 3–6-12 months thereafter. The Medical Outcomes Study 36-Item Short-Form Health Survey (SF-36) will be used to assess general health-related quality of life status. Cancer-specific quality of life is evaluated by the core quality of life (QLQ-C-30) questionnaire developed by the European Organization for Research and Treatment of Cancer (EORTC). The Head and Neck cancer-specific questionnaire (H&N-35) is a supplementary module of the QLQ-C-30 questionnaire that includes 35 head and neck cancer-specific items. Finally, the Spanish version of the Shoulder and Pain Disability Index (SPADI) is a self-administered questionnaire that covers two aspects, one for pain and the other for functional activities, with lower scores representing less pain or disability.

### Supervised exercise intervention

The programme operates throughout the year and is a free 12-week, small group exercise programme supervised by specially trained instructors including exercise physiologists, physiotherapists and nurses. Participants are required to participate in supervised exercise sessions three times a week in the exercise laboratories, (primary health-care centres and Cruces University Hospital/Biocruces Bizkaia Health Research Institute). Twice a week, the sessions include a combination of strength exercises and moderate-to-high intensity aerobic exercise, and they last approximately 1–1¼ hours. The third session does not include aerobic exercise, and lasts 30 to 45 min. Strength exercises are conducted with free-weights (to provide a quantifiable measurement of progressive overload), elastic bands and suspension training, with the intention that the patients should learn how to train on their own. [22].

The strength exercises target five of the major upper and lower body muscle groups, as well as core exercises. Progression from static exercises towards more dynamic exercises is encouraged, aiming to activate more muscle mass. Among the main parameters that can be modified, the actual number of repetitions performed in a set, in relation to the maximum number that can be completed (i.e., proximity to muscle failure), recently called “level of effort”, will be used to individualise the strength exercise intensity, maximise the suitability of the exercise for each patient, and optimise induced neuromuscular fatigue [23, 24].The target intensity is adjusted from 9 to 12 repetitions out of the 18 repetitions that could be completed (written as 9–12 [18]), which is equivalent to ~ 60% of 1 repetition maximum (1RM) using 2 sets during the first 4 weeks, to 4 sets of 7–10 [14], which is ~ 70% of 1RM in the last 4 weeks of the programme.

The aerobic exercise component includes 20–25 min of at least moderate intensity for 8-min periods alternating with 2-min lower-intensity periods during the first month, moving toward higher-intensity 5-min intervals by the third month (Fig. 2). The exercise intensity zones are tailored to each patient by the estimated maximum heart rate using the Eq. (220—age) [25] and applying specific intensity boundaries based on the heart rate reserve (HRR), defined as the difference between the resting heart rate and maximum heart rate. %HRR has been adopted by the American College of Sports Medicine as the gold standard for indirect assessment of exercise intensity [26, 27]. Every exercise session will be monitored with a heart rate monitor, teaching the patients to self-manage their exercise sessions with respect to the prescribed target intensities; the target intensity is between 40 and 85% of HRR [26, 27]. The perceived level of effort is to be recorded using the Borg Rating of Perceived Exertion (RPE) scale from 0 (rest) to 10 (maximal effort) [28], with the target intensity progressively increasing from 3 to 5–6 points (Table 3).

